#### Training and remuneration of personnel

Chauffeurs of the GP cooperatives will be trained in using portable monitors for vital sign measurement and other study procedures. At the GP cooperative in Ede, the chauffeurs will also be trained in the measurement of POC-lactate, as GPs will collect the venous blood samples themselves occasionally. The laboratory assistants and nurses who will be on call for the collection of the blood samples will also be trained in the POC–lactate measurement and other study procedures, including the obtaining of written informed consent. Attending GPs will be informed by an information letter by mail and hard copy at the GP cooperative. Leaflets with a summary of the study procedures will also be available.

#### Follow-up

The total follow-up time is 30 days (see Fig. 1). Patients will be asked to complete the EQ5D-5L questionnaire [22] at the end of follow-up to report on their health status: (1) at the day of completion of the questionnaire, (2) before the onset of the recent disease episode (i.e. their health status of at least 1 month ago), and (3) for the worst day they remember from their recent disease episode. Furthermore, patients will be asked to report on consumption of medical resources during the 30-day follow-up period. In case of no response to the questionnaire after 1 week, patients will be contacted once by telephone as a reminder.

**Fig. 1 Fig1:**
[figure not shown]
Summary of study procedures

#### Data extraction

Relevant medical information will be obtained from the patient’s (regular) GP, the GP cooperative, and the hospital. Information from all hospital admissions in the 30-day follow-up will be retrieved, first by digital search in the local hospital and secondly by manual screening of the GP record for admissions in other hospitals. Medication use and comorbidities before inclusion will be retrieved from GP electronic records, as well as information on any subsequent contacts. The medical record of the assessment at the time of inclusion will be retrieved from the GP cooperative. The following data from the electronic medical record of the hospital will be collected: full reports from ED and hospital discharge; date and time of ED visit, hospital admittance, and discharge (including type of ward); vital signs, EMV score, leucocyte count, thrombocyte count, creatinine, bilirubin, CRP, and lactate measured in the first 72 h after inclusion; cultures taken in the first 72 h after inclusion; radiodiagnostic procedures in the first 7 days after inclusion; antibiotic prescriptions during hospitalisation; and intravenous volume therapy in the first 72 h (defined as more than 1.5 l of fluids in 24 h).

### Sample size

In total, 12 candidate predictors are chosen for the development of the prediction model (Table 1). Using the rule of thumb of 10 events per variable [23], we need 120 patients reaching the primary outcome “sepsis within 72 h after inclusion” in the final dataset. Prior to the start, the prevalence of sepsis based on previous research and literature was estimated to be around 12%. However, preliminary data analysis from the patients included in the study so far indicates the prevalence of sepsis in the study cohort to be around 30–40%. After the first 100 cases will be assessed by the expert panel, we will determine the final target sample size.

### Statistical analyses

#### Descriptive statistics

We will use a combination of IBM SPSS Statistics and R Statistical Software for all analyses. We will start with descriptive analyses on baseline characteristics (age, sex, comorbidities, vital sign measurements and other clinical features, blood tests results, baseline EQ5D-5L score), final diagnosis, hospital admission, ICU admission, length of stay, EQ5D-5L compared to baseline, and 30-day mortality. Results will be stratified based on whether patients do or do not meet the primary outcome sepsis.

#### Data cleaning

Range and distribution of all continuous variables will be graphically inspected, and any outliers (more than three standard deviations from the mean) will be discussed and corrected or removed in case of a data recording error. Any missing data on clinical features or blood tests will be accounted for by applying multiple imputation techniques. Prediction model development and performance will be analysed using the imputed datasets.

#### Development of the prediction model

A multivariable penalized logistic regression model will be developed, based on the variables listed in Table 1, for predicting the primary outcome (sepsis within 72 h after inclusion). We will use a two-stepped approach entering and selecting clinical features first, and blood tests second. In both steps the selection of predictors will be based on a stepwise backward selection, using change in Akaike information criterion (AIC) for selecting the preferred model [24]. The goal is to generate an efficient model by eliminating variables that contribute little to the model’s performance, requiring only measurement of the most important variables in clinical practice.

Continuous predictors in the model will be assessed for linear relationship with the logit of the primary outcome. Transformation of the data and splines will be used if deemed appropriate based on distribution of the data.

The resulting prediction model will be the most accurate prediction model, by making use of continuous measurements of predictors and reflecting non-linear relationships by transformations or splines (optimal model). To make this model workable in daily clinical practice without electronic aids, a second model will be derived (clinical practice model) by categorising or stratifying predictors. Cutoffs for categorisation will be based on a combination of known and commonly used thresholds in clinical practice and optimal thresholds based on the data. This model simplification is likely to induce a performance drop with regard to the full model, which will be assessed during the analysis.

The above procedures will result in the following three models: (1) optimal model with clinical features only, (2) optimal model with clinical features and blood tests, (3) simplified model (with clinical features and blood tests).

#### Performance of the prediction model

The performance of all three models will be determined based on their discrimination and calibration. Discrimination will be evaluated based on the area under the receiver-operator characteristic (AUROC). Calibration will be assessed by plotting observed and expected probabilities and inspecting this plot graphically. Measures of calibration will include calibration slope, calibration in the large, observed/expected (O/E) ratio, and the Brier score [25]. We will perform internal validation for all three models by using a bootstrap simulation. The resulting distribution will reflect optimism and the degree of overfitting [26].

The SIRS criteria, NEWS score, and qSOFA score will be calculated for all individuals in the TeSD-IT study. Diagnostic performance of the existing models will be determined by calculating the same measures of discrimination and calibration as described in the sections above and comparing these with the three models that were developed.

To assess the added value of the prediction models on top of usual care, other outcomes than sepsis will be considered. This is crucial for gaining insight in the net benefit of using the clinical prediction rule in daily practice. For example, when a patient is predicted as non-sepsis by the model, but the patient was referred by the GP, improvement compared to care as usual is only the case if hospital treatment was not needed according to the expert panel. To assess the added value, the proportion of reclassifications within the original contingency tables will be presented for the following outcomes: (1) the gut feeling of the visiting GP that “something is wrong”, (2) the assessment of the visiting GP for the likelihood of sepsis, and (3) the decision of the visiting GP whether or not to refer the patient to the hospital.

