To limit the workload for the experts, we will appoint three expert panels, each comprising a GP, an emergency physician, and an internist(-intensivist). Each case will be assessed by one panel. All relevant information from medical records from the GP and the hospital when applicable will be presented to the panel (see Additional file 1). If there is no consensus on the primary outcome, the case will be discussed in a face-to-face consensus meeting with all three experts to determine the final outcome. Interobserver agreement between the three panels will be assessed in a selection of 10% of the cases that will be assessed by all panels. Besides the dichotomous primary outcome “sepsis within 72 h”, the likelihood of sepsis will be assigned a numerical score between 0 and 10. This gives information on the remaining uncertainty regarding sepsis classification, providing insight in the degree of bias that may be introduced when calculating diagnostic accuracy measures using dichotomous sepsis classification [21]. Furthermore, the need for hospital treatment is scored between 0 and 10 by the expert panel as a secondary outcome. An average score above 5 will be regarded as a patient that should best be referred to the hospital immediately by the GP and a score ≤ 5 as a patient that does not have to be referred immediately.

Other outcome measures are hospitalisation (length of stay and type of care: ICU or regular ward), maximum SOFA score in the first 72 h, 30-day all-cause mortality, final diagnosis, and medical costs.

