#### Procedure during home visit

All patients will receive usual care. Patients will be screened for eligibility during home visits by the attending GP of the GP cooperative. Verbal informed consent will be obtained from the patient or his legal representative. The GP will be (routinely) accompanied by a chauffeur during the home visit. The chauffeurs are used to practically assist the GP during the visit. Portable monitors (Philips intelliVue MP2 or X2) will be available to record peripheral oxygen saturation, automated blood pressure, and heart- and respiratory rate by three lead electrodes on the chest.

The GP will record the assessment of the candidate predictors in a case report form. In addition, the GP will record if he/she has a gut feeling that “something is wrong” and will provide the likelihood of the presence of sepsis at inclusion on a scale from 0 to 10.

All study materials will be taken to the patient’s home in a study bag. The venous samples will be collected by either the GP or an on-call laboratory assistant or nurse within 1 h after inclusion, with a maximum of 8 h. Written informed consent will be obtained prior to the collection of the blood samples. In case the patient is referred to the hospital and the blood samples are not collected by the GP, the study bag will be transported with the patient to the ED. Subsequently, the laboratory assistant on call will visit the patient in the hospital and collect the blood samples. Three blood tubes will be collected: 10 ml for serum, 10 ml for EDTA plasma, and a 2-ml heparin tube. Lactate will be measured immediately afterwards from a single drop of blood taken from the heparin tube, using the StatStrip Xpress (Nova Biomedical) POC test. The remaining blood samples will be taken to the hospital laboratory and divided into six samples of serum and six samples of EDTA plasma. The aliquots will be temporarily stored at the local laboratory at < − 70 °C. Two samples (1 ml serum and 1 ml EDTA plasma) will be transported to the Jeroen Bosch Hospital for CRP and PCT analyses, and the remaining samples (5 × 0.5 ml serum and 5 × 0.5 ml EDTA plasma) will be stored for 15 years at < − 80 °C at the UMC Utrecht for potential future testing.

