The expert panels will be instructed to use the SOFA score (increase, due to infection, of ≥ 2 points from baseline) to define the primary outcome “sepsis within 72 h after inclusion”. This is consistent with the Sepsis-3 consensus definition and leads to an objective and reproducible endpoint in the absence of a gold standard. However, this approach introduces the risk of incorporation bias. Parameters included in the SOFA score are more likely to be predictive of sepsis in our model. However, the blood tests (CRP, lactate, and procalcitonin) are not included in the SOFA score, which limits the risk of incorporation bias for these tests. Furthermore, vital signs measured in the first 72 h will be used to calculate the SOFA score and not only at the time of inclusion.

Patients will receive a questionnaire at day 30 measuring EQ5D-5L. The results may be biased due to selective response and poor recall due to sepsis- or age-related cognitive impairment. Imputation of the missing answers on the questionnaires will reduce this form of bias as much as possible. Furthermore, the development of the clinical prediction rule is not affected, as the patient questionnaires will only be used for the cost-effectiveness analyses

To compare the performance of the new clinical prediction rule with usual care, not only the decision to refer the patient to the ED, but also the assessment of the GP of the likelihood of sepsis on a scale from 0 to 10 and the presence of a “gut-feeling something is wrong” will be used. We will examine if the prediction rule will outperform those assessments of the GP in order to likely improve the usual care.

Only three candidate blood tests were selected for the development of the prediction rule. Various other biomarkers have promising diagnostic and/or prognostic properties in patients with suspected sepsis [29, 30]. At the start of this study, sufficient evidence of the additional diagnostic and/or prognostic value above lactate, CRP, and PCT was lacking. However, sufficient blood samples will be stored for retrospective testing of multiple additional biomarkers.

Although to our best knowledge no clinical prediction rules for sepsis in primary care were previously developed, several sepsis screening tools were published for the ambulance setting [31]. However, none of those have adequate inclusion criteria, data collection, and clinically relevant endpoints for use in the primary care setting.

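### The only comparison stated for the GP's 0–10 sepsis likelihood is reclassification in contingency tables; this discards ranking information and lets unmatched cuts, rather than discrimination, decide whether the rule looks better

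*Protocol article*

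**What the plan says.** Under Procedure during home visit, the GP "will provide the likelihood of the presence of sepsis at inclusion on a scale from 0 to 10". This is an ordered score with 11 levels.

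Under Performance of the prediction model, the article sets out two kinds of comparison:

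- The three new models are assessed by AUROC and calibration. SIRS, NEWS and qSOFA follow suit: "Diagnostic performance of the existing models will be determined by calculating the same measures of discrimination and calibration".
- For usual care, "the proportion of reclassifications within the original contingency tables will be presented for the following outcomes". Three GP assessments are then listed: gut feeling, "the assessment of the visiting GP for the likelihood of sepsis", and the referral decision.

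The Discussion says that usual care will be represented partly by "the assessment of the GP of the likelihood of sepsis on a scale from 0 to 10", and continues: "We will examine if the prediction rule will outperform those assessments of the GP in order to likely improve the usual care".

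The article gives no cut for the GP's likelihood or for the model probability. The one cut on a 0–10 scale belongs to the expert panel's rating of need for hospital treatment: "An average score above 5 will be regarded as a patient that should best be referred to the hospital immediately by the GP".

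**The concern.** Gut feeling and referral are yes/no, so a contingency table suits them. The likelihood score is graded, and so is the model's predicted probability. To enter a reclassification table, both must be put into categories. Two things follow.

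1. Patients on the same side of a cut become indistinguishable. A real difference in discrimination is then estimated less precisely than the same data allow.
2. The table compares two operating points. If the cuts flag different proportions of patients, the net result mixes the choice of cut with the quality of the score.

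The existing scores are compared on their full scale, while the graded measure of the GP's own judgement is not. Yet it is against the GP that the Discussion asks whether the rule would improve care. A statement that the rule outperforms the GP's likelihood could therefore come from the cuts alone.

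**Working it through.** **Step 1: the plan's own figures.** Sample size: 12 predictors × 10 events = 120 events. At the outcome rate of 0.35 given in the Discussion, 120 / 0.35 = 342.9, which agrees with the stated figure of about 350. The alternative calculation with rMPSE 0.09 was not checked, because its coefficients are not given. No power, significance level or effect size is stated for the comparison with the GP.

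**Step 2: why the cuts matter, in closed form.** Net reclassification = (sensitivity of rule − sensitivity of GP) + (specificity of rule − specificity of GP). Assume two normal scores, each with AUROC 0.80.

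- Separation: d = √2 × Φ⁻¹(0.80) = 1.190.
- Cut at the midpoint: sensitivity = specificity = Φ(0.595) = 0.7241; sum 1.4482.
- Cut at 90% sensitivity: specificity = Φ(1.190 − 1.2816) = 0.4636; sum 1.3636.
- Net reclassification between the two: 1.4482 − 1.3636 = 0.085, although discrimination is identical.

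The simulation below agrees: with the model cut at 90% sensitivity and the GP at ≥5 or ≥6, net reclassification is −0.073 to −0.074. The GP cut lies slightly off the midpoint, which accounts for the remaining 0.011–0.013.

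**Step 3: simulation set-up.** From the document: about 350 patients at 0.35, i.e. 350 × 0.35 ≈ 122 with sepsis and 228 without. Assumed: bivariate normal scores within each group, the GP score cut to 11 levels, and the AUROCs, correlations r and cuts shown. A result favours the rule if z > 1.96. A paired DeLong test on the uncut model score and 0–10 GP score is set against a z-test of net reclassification after cutting both.

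**Step 4: equal AUROCs.**

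| Setting | Favours rule |
|---|---|
| AUROC 0.80, r = 0.5: paired AUROC test | 3.6% |
| Same, model at midpoint, GP ≥5 or ≥6 | 4–5% |
| Same, model at midpoint, GP ≥4 or ≥7 | 32–36% |
| Same, model at midpoint, GP ≥3 | 95% |
| Same, model at 90% sensitivity, GP ≥5 | 0% (favours GP in 26%) |
| AUROC 0.75, r = 0.4: paired AUROC test | about 3% |
| Same, matched positive rates | 2–3% |
| Same, model flags 35%, GP ≥3 | 76–87% |
| Same, model flags 35%, GP ≥8 | 59–77% |

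The ranges in the last two rows come from different spacings of the 11 levels.

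**Step 5: rule truly better, near-middle cuts (model at its midpoint, GP ≥5 / ≥6).**

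| AUROC rule v GP | r | Paired AUROC | Table | Loss (points) |
|---|---|---|---|---|
| 0.80 v 0.72 | 0.3 | 74% | 55% / 51% | 19–22 |
| 0.80 v 0.72 | 0.5 | 87% | 61% / 61% | 26 |
| 0.80 v 0.70 | 0.3 | 90% | 71% / 72% | 18–19 |
| 0.80 v 0.70 | 0.5 | 95% | 79% / 77% | 16–17 |
| 0.80 v 0.75 | 0.5 | 51% | 34% / 31% | 17–20 |
| 0.85 v 0.75 | 0.5 | 98% | 89% / 86% | 10–13 |

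Setting the model cut to the GP's positive rate instead (0.80 v 0.72, r = 0.3–0.5, GP ≥5 or ≥6) gave 75–86% against 44–57%, a loss of about 25–35 points. Over all cut pairs tried, the change ran from a loss of about 74 points to an apparent gain of about 49. The gains are not real: the same unmatched cuts favour the rule when the AUROCs are equal (Step 4).

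**The case against.** The case on the other side has four parts.

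- **No test is planned.** The proportions are to be presented, without a significance level or decision rule. This stands. A reader might infer that the plan forfeits a definite amount of power; one matched-cut scenario (0.80 v 0.72, r = 0.4) gives 78% against 50%, or 28 points. The document supports no such figure, since the AUROCs, correlation, cuts and test are all assumed. Power here only expresses lost precision.
- **The paragraph asks about decisions.** It considers outcomes other than sepsis, and its example judges a reclassified patient by whether the expert panel thought hospital treatment was needed. That question needs categories. This also stands, and is a reason to keep the tables. It does not supply a comparison of discrimination with the GP's likelihood.
- **False superiority needs unmatched cuts, and the plan proposes none.** Correct. A reader might infer that the study will wrongly favour the rule, but at matched cuts there is no material inflation, and the error can also run against the rule. The cuts may be set in a fuller document, so their absence is not the point. Matching would remove the bias but not the loss of information.
- **The Discussion does not confine the examination to a table.** True, but the analysis section states no other method for this score, while it gives AUROC to every other graded predictor it compares with the rule.

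The stakes are also bounded: the likelihood is one of three GP comparators, and the article requires external validation before implementation.

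**Conclusion.** The point holds as a weakness in a stated method. The GP's graded likelihood is given a coarser comparison than the existing scores, and that comparison can depend on the cuts more than on discrimination.

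The size is illustrative. With assumed AUROCs of 0.80–0.85 for the rule and 0.70–0.75 for the GP, and correlations of 0.3–0.5, near-middle cuts cost roughly 10–35 points of power. With equal AUROCs of 0.75 or 0.80, badly unmatched cuts favoured the rule in about 59–95% of simulated trials, against about 3–4% for the paired AUROC test. The simulations treat the model as fixed. They leave out overfitting in the development data, which would favour the rule further if uncorrected.

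The planned analysis is not shown to reach a wrong conclusion. The change is worth making because it is nearly free and the data are already collected.

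**What to change.** In Performance of the prediction model, add the AUROC of the GP's 0–10 likelihood for sepsis within 72 h. Report its paired difference, with 95% CI, from the AUROC of each of the three models in the same patients. Correct the model AUROCs for optimism with the bootstrap already planned; the apparent AUROC in the development data would favour the rule. The paired difference and interval would be new wording, since for SIRS, NEWS and qSOFA the article says only that the measures will be compared.

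Base any statement that the rule discriminates better than the GP's likelihood on this difference. Keep the reclassification tables for gut feeling, referral and the question of need for hospital treatment. If a table for the likelihood score is kept, present it as descriptive, with the model cut set to flag the same proportion of patients as the GP cut.

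Cost: a sentence or two of wording and a little more analysis, with no new data and no extra patients. An AUROC difference is less directly clinical than a table, but the tables are still shown.

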## Discussion

The TeSD-IT study is a diagnostic and prognostic study, designed for the development of a clinical prediction rule for the early recognition of sepsis in primary care. A limited number of nine clinical parameters and three blood tests were selected. This will enable us to construct the model using multivariable logistic regression techniques with 120 events included in the dataset. We realise the validity of rule of thumb of 10 event per variable is debated [27]. However, using an alternative sample size calculation suggested by van Smeden [28] results in a similar identical sample size of about 350 patients in case of 12 variables, an outcome rate of 0.35, and rMPSE set at 0.09. We have chosen to recruit patients in the setting of out-of-hours home visits performed by a GP. In this setting, GPs frequently encounter seriously ill patients in whom they instantly have to decide whether or not to refer the patient (immediately) to the hospital. A methodological advantage is that the required sample size is substantially lower than in other primary care settings with a lower incidence of sepsis. However, external validation in other settings and populations will be needed before implementing the clinical prediction rule more broadly.

The diagnosis of sepsis is not straightforward. In 2016, new consensus definitions for sepsis were published, which we try to implement as well as possible. As both the presence of infection as well as organ failure can be equivocal, we will use expert panels to determine the final outcome. The outcome should be clinically relevant for the GP. The rationale of the timeframe of 72 h is that patients who are found septic within this period after GP assessment would likely benefit from immediate hospital referral. Not all patients with organ failure need hospital treatment to recover, and not all patients with severe infections that are treated with intravenous antibiotic therapy have signs of organ failure. However, we believe the diagnosis of sepsis based on the Sepsis-3 definitions is the most relevant endpoint for GPs to differentiate between patients who are likely to benefit from immediate hospital treatment and patients who might be treated at home successfully. The expert panel will also rate the need for hospital treatment for every patient, regardless of the diagnosis. This will enable us to evaluate the effect of the new clinical prediction rule on medically unnecessary referrals.

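### The rule is compared with GP judgement in its own development data, with no optimism correction stated for the reclassification tables, which favours the rule

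*Protocol article*

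**What the plan says.** All of this is in the Protocol article.

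- **Model building** (Development of the prediction model): "A multivariable penalized logistic regression model will be developed". Predictors are chosen by backward selection on AIC, clinical features first and blood tests second. For the simplified model, predictors are categorised at cut-offs that combine commonly used "thresholds in clinical practice and optimal thresholds based on the data".
- **Internal validation** (Performance of the prediction model): discrimination and calibration measures are named, followed by a general statement that all three models will be internally validated by bootstrap.
- **Comparison with the GP** (same section, later): for gut feeling, the GP's likelihood of sepsis and the referral decision, "the proportion of reclassifications within the original contingency tables will be presented for the following outcomes". In the worked example about referral, improvement is judged by the panel's rating of need for hospital treatment.
- **Purpose** (Discussion): "We will examine if the prediction rule will outperform those assessments of the GP in order to likely improve the usual care".

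The GP's gut feeling and likelihood score are recorded at the home visit (Procedure during home visit). The abstract and the Discussion both say that external validation must come before the rule is used.

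**The concern.** The two sides of the comparison are treated unequally. The rule's predictors, coefficients and some of its cut-offs are chosen to suit these patients, so its errors in the same patients understate its errors in new ones. The GP's judgement was given at the visit and was fitted to nothing. A reclassification table built on the development data therefore carries optimism on the rule's side only, unless it is corrected. The article states no such correction for these tables.

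It also leaves open which predicted risk separates sepsis from non-sepsis. If that threshold were set after looking at the data, the optimism would grow.

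This is the analysis meant to show whether the rule adds anything to usual care, so a systematic tilt here bears on one of the study's main messages.

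**Working it through.** **1. The plan's own size.** The Sample size section says: "Using the rule of thumb of 10 events per variable [23], we need 120 patients reaching the primary outcome". Check: 12 × 10 = 120 events. At the Discussion's outcome rate of 0.35, 120 / 0.35 = 342.9, so 343 patients. This agrees with the stated "sample size of about 350 patients in case of 12 variables, an outcome rate of 0.35, and rMPSE set at 0.09" to within about 2%. At the 30–40% prevalence seen so far, the range is 120 / 0.40 = 300 to 120 / 0.30 = 400. The figure of 350 was not re-derived from the prediction-error target, because the article does not give the formula.

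**2. Measure.** Youden's J = sensitivity + specificity − 1. Optimism = J in the development patients − J of the same rule in 20,000 new patients.

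**3. Set-up.** From the article: 12 candidates (9 clinical, 3 blood tests), about 350 patients, prevalence 0.35, two-step backward AIC selection and a penalised fit. The following are assumptions:
- Predictors are independent and normal, with log-odds per SD of 0.8, 0.6, 0.5, 0.4, 0.3, 0.2, 0.1, 0, 0 (clinical) and 0.5, 0.3, 0.1 (blood tests). These are the larger effects; the smaller effects are 0.75 times these.
- The simplified rule dichotomises each retained predictor and uses a light ridge penalty. Established cut-offs are fixed at the predictor's mean. In the mixed case, every second retained predictor has a fixed cut-off and the others a data-optimal one. In the data-based case, all are data-optimal.
- Patients are classified either at the score that maximises J in the development data or at a fixed predicted risk of 0.35. The latter is a device of the simulation, not a recommendation.
- Need for hospital treatment is present in 85% of patients with sepsis and 25% of those without.
- There were 160 simulated studies with larger effects and 100 with smaller effects.

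**4. Optimism of the simplified rule (apparent − true J).**

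| Effects | Cut-offs | Sepsis, data-chosen cut | Sepsis, fixed risk | Hospital need, data-chosen cut | Hospital need, fixed risk |
|---|---|---|---|---|---|
| Larger | Established | 0.402 − 0.321 = 0.081 | 0.373 − 0.327 = 0.046 | 0.222 − 0.180 = 0.042 | 0.204 − 0.184 = 0.020 |
| Larger | Mixed | 0.453 − 0.314 = 0.139 | 0.426 − 0.317 = 0.109 | 0.256 − 0.177 = 0.079 | 0.237 − 0.179 = 0.058 |
| Larger | Data-based | 0.502 − 0.311 = 0.191 | 0.477 − 0.317 = 0.160 | 0.275 − 0.175 = 0.100 | 0.263 − 0.178 = 0.085 |
| Smaller | Established | 0.341 − 0.238 = 0.103 | 0.311 − 0.245 = 0.066 | 0.187 − 0.128 = 0.059 | 0.170 − 0.132 = 0.038 |
| Smaller | Mixed | 0.390 − 0.238 = 0.152 | 0.365 − 0.242 = 0.123 | 0.217 − 0.127 = 0.090 | 0.201 − 0.130 = 0.071 |
| Smaller | Data-based | 0.444 − 0.242 = 0.202 | 0.422 − 0.246 = 0.176 | 0.242 − 0.131 = 0.111 | 0.229 − 0.133 = 0.096 |

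For comparison, the model with continuous predictors gives 0.494 − 0.409 = 0.085 (larger effects) and 0.419 − 0.321 = 0.098 (smaller) at the data-chosen cut. At the fixed risk it gives 0.462 − 0.414 = 0.048 and 0.385 − 0.328 = 0.057. This is close to the simplified rule with established cut-offs. The simplified rule becomes the more exposed one when some cut-offs are searched on the data.

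**5. What this does to a comparison with the GP.** The simulated GP has sensitivity = specificity = 0.5 + J/2 and errs independently of the rule given the outcome. Without bias, a GP with the same true J as the rule should look worse in about 50% of studies.
- Equal true J, sepsis: the rule looks better in 71–92% of studies (established), 90–96% (mixed) and 99–100% (data-based).
- Equal true J, hospital need, data-chosen cut: 72–90%.
- GP truly better by 0.20 in J, sepsis, data-chosen cut: the rule still looks better in 4–10% (established), 18–26% (mixed) and 46–54% (data-based).

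**6. Does the correction work?** Selection, cut-off choice and classification were repeated in each bootstrap sample, in a quarter of the simulated studies, at the data-chosen cut. Values are apparent, corrected and true J.
- Larger effects: 0.40, 0.33, 0.32 (established); 0.45, 0.33, 0.31 (mixed); 0.50, 0.36, 0.31 (data-based).
- Smaller effects: 0.34, 0.27, 0.24; 0.39, 0.27, 0.24; 0.44, 0.30, 0.24.

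**The case against.** The best defence is that the article already plans a bootstrap for all three models, says that it is meant to reveal overfitting, and does not exclude the reclassification tables. Which statistics are recomputed in each bootstrap sample is a detail that a full protocol or analysis plan may hold. That stands in part. A reader might infer that the bootstrap covers discrimination and calibration only, but this rests on the order of the paragraphs. What can be said is that no correction is stated for an analysis that the article does specify.

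Other points also limit the concern:
- A reader might infer that the rule's positivity threshold is tuned on the data. The data-based cut-offs in the text categorise predictors; the classification threshold is simply not given.
- The referral example is scored on need for hospital treatment, to which the model is not fitted. Optimism is smaller there, but not nil.
- Established cut-offs are part of the plan, and three of the twelve candidates are binary with nothing to search. The fully data-based rows therefore overstate the planned rule.
- The fit is penalised. A light penalty was included in the simulated simplified rule and the bias remained; a stronger one could reduce it.
- A reader might infer that missed sepsis and unnecessary referral are given equal weight. No pooled or weighted figure is stated, and the example given is specific to one direction.
- The GP's likelihood is on a 0 to 10 scale, and no cut is given for it. A cut chosen on the data would put some optimism on the GP's side of that one comparison.

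The call for external validation limits the harm to practice. It does not correct the comparison that this study will itself report.

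**Conclusion.** The concern holds in a limited form. As written, the comparison with GP judgement is made in the development data, with no stated optimism correction and no fixed classification threshold, so it leans towards the rule.

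Under the assumptions above, optimism in J for sepsis is about 0.05 to 0.10 with established cut-offs and 0.11 to 0.15 with mixed ones, the case closest to the plan. On need for hospital treatment it is about 0.04 to 0.11 at a data-chosen classification cut, across the three cut-off scenarios, and 0.02 to 0.10 at a fixed one.

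It would go too far to say that the rule will appear to beat usual care through overfitting alone. That depends on the true gap: with mixed cut-offs, a GP better by 0.20 in J would still usually look better. Effect sizes, predictor distributions, penalty strength and the link between sepsis and hospital need are all assumed, so the figures are a range and not a forecast for this cohort.

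**What to change.** - Prespecify the predicted risk or score at which the rule classifies a patient, before the comparison with the GP is run.
- Prefer established predictor cut-offs where they exist. Table 1 names no source score or guideline for CRP, lactate or procalcitonin, so some data-based choice may remain.
- State that AIC selection, any data-based choice of cut-offs and the reclassification tables are all repeated within every bootstrap sample.
- Report optimism-corrected reclassification separately for patients with and without the panel outcome, once for sepsis and once for need for hospital treatment.
- Corrected net benefit may be added as a supplement; it is not essential to the repair.

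The cost is some extra code in a bootstrap that is already planned and a less favourable reported performance. No new data are needed. In the simulations the correction removed most of the bias but not all of it, so a remaining lean towards the rule should be acknowledged in the report.
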